## 6 Statistical analysis

Primary analysis of the BGSi will be completed on an ITT basis at the 3 month endpoint using mixed effect models. Stratification variables will be incorporated into the model and other potential factors that could affect the results will be determined a priori and considered for inclusion in the models. All treatment effect estimates will be presented with 95% confidence intervals and 5% level of significance will be used. Analysis of secondary outcomes will follow the same analysis model as the primary analysis where possible. Binary outcomes will be analysed using multi-level logistic regression. Exploratory analysis will be conducted to investigate the effect of phenotypes and comorbidities on the outcome.

Where possible missing data will be minimised however a maximum-likelihood multiple imputation approach will be used with a sensitivity comparison of complete case dataset. The planned analysis will be specified in the statistical analysis plan (SAP), any deviations from the analysis plan will be justified and fully documented in the results report.

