## **4. STATISTICAL PRINCIPLES**

All those randomised will be included in the analysis based on an intention to treat (ITT) principal.

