## 4.6 MISSING DATA

Every effort will be taken to minimise missing data. If imputation (e.g., mean substitution) is part of the validated measure it will be performed, see Appendix 1 for measure scoring rules. Where there are no missing data rules for the measure, if the number of missing items on an outcome is 20% or less, then the missing value for the item will be substituted by the individual's mean score for the remaining items on the scale (Bono, Ried, Kimberlin and Vogel 2007). If there are more than 20% missing items in the scale the outcome measure will not be calculated for the participant at that time point and multiple imputation methods will be used.

In accordance with the recommendations of Jakobsen, Gluud, Wetterslev and Winkel (2017), if the proportion of missing data is less than 5%, no imputation of missing data will be performed, and analyses will be based on complete cases. If the proportion of missing data is equal to or greater than 5%, a missing completely at random test devised by Little (1998) will be performed to assess whether the data is missing completely at random (MCAR). If this test indicates that data is missing completely at

random then analyses will be based on complete cases, else independent t-tests and Chi-square tests will be conducted to investigate whether the data is missing at random (MAR). If these tests suggest that the missing data is MAR, then predictive mean matching multiple imputation methods will be employed. Otherwise, additional modelling guided by clinical knowledge would be required to simulate the missing data mechanism and impute the missing data.

For multiple imputations, the number of imputations completed will be dependent upon the percentage of missing data (White et al., 2011). The missing outcome measures will be imputed using Allocation Group and Stratification factors (Site) and other variables that are deemed to be predictors of missingness. Variables will be assessed for being predictors of missingness by running statistical tests on completers versus non completers and evaluating if any differences are present between the two.

Variables to be assessed as predictors of missingness include;

- Age
- Sex
- Ethnicity
- Education
- Disability
- Occupation
- Drugs
- CV19 (diagnosed conditions (before/during))
- Number of vaccines
- Cognition

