If MI is used, complete case analysis will also be conducted as a sensitivity analysis to check the assumptions of the MI models, see section 6.8. In line with the recommendations of Jakobsen et al (2017), if more than 40% of data is missing for an outcome measure the data will not be imputed and an analysis will be conducted on complete cases, though the results of the analysis will be interpreted tentatively.

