### **5.2 TIME POINTS OF OUTCOMES MEASURES**

Outcome measures are collected at baseline, 3 months and 6 months post-randomisation. Appendix 1 contains a list of all data collected during the study.

The primary outcome is participant-reported goal attainment at 3 months post-randomisation. This will also be collected as a secondary outcome at the 6 month post-randomisation follow up. This will be collected using the Bangor Goal Setting Interview (BGSi).

Secondary outcomes will be:

- Goal Satisfaction Scale ((using the Bangor Goal Setting Interview Scale)
- Cognitive function (tested using the cognitive batteries employed for Workstream 1)
- Quality of life (EQ-5D-5L)\*
- Life Space Assessment
- Social Functioning (SF-DEM)
- Instrumental Activities of Daily Living (IADL) Scale
- Generalised Anxiety Disorder Assessment (GAD-7)
- Patient Health Questionnaire (PHQ-8)
- Chalder Fatigue Scale
- Pittsburgh Sleep Quality (PSQI)
- DePaul Symptom Questionnaire – Post-Exertional Malaise (DSQ-PEM).
- Client Service Receipt Inventory (CSRI)\*

Cognitive function will be assessed using three complementary assessments (expanded below), to maximise understanding of cognition

- Cognitive function assessment 1 – battery of Cognitive tests
  - The Repeatable Battery for the Assessment of Neuropsychological Tests (RBANS)
  - The Delis-Kaplan Executive Function System: The Trail Making Test (Condition 2: Number Sequencing & Condition 4: Number-Letter Switching)
  - The Delis-Kaplan Executive Function System: Colour-Word Interference
  - The Delis-Kaplan Executive Function System: Phonemic Fluency
  - Wechsler Adult Intelligence Scale III: Digit Span
  - Test of Premorbid Functioning (TOPF)
- Cognitive function assessment 2 – online battery of cognitive tests
  - Gorilla
  - 4 Mountains (4MT)
- Cognitive function assessment 3
  - Neotiv suite

\*Health economic data not being analysed at by NWO.

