## 6.6 ANALYSIS OF PRIMARY OUTCOME

The primary outcome, the BGSi (attainment score) at the 3 months, will be analysed using a multi-level (mixed effect) linear regression model to assess the differences between the two treatment arms. Stratification variables (Site) will be incorporated into the model as a random effect along with gender, age (continuous), years of education (continuous) and RBANS composite score at baseline as fixed factors. Baseline BGSi attainment score will also be incorporated to account for any differences at baseline.

The BGSi at 6 months will be analysed as a secondary outcome using the same model structure as the primary. Unadjusted (section 6.5) and adjusted results will be presented with associated 95% confidence intervals.

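### For 6-month outcomes the SAP never explicitly uses the observed 3-month score, and above 40% missing it falls back on complete cases alone

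*Combined protocol and SAP*

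**What the plan says.** SAP 5.2 sets the visits: "Outcome measures are collected at baseline, 3 months and 6 months post-randomisation". The primary model in SAP 6.6 is for the 3-month BGSI attainment score. Its only random effect is site ("Stratification variables (Site) will be incorporated into the model as a random effect"), so multi-level refers to sites and not to repeated scores on one person. For the later visit, "The BGSi at 6 months will be analysed as a secondary outcome using the same model structure as the primary". SAP 6.7 repeats that structure for the other secondary outcomes. SAP 4.3 calls all secondary outcomes exploratory.

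SAP 4.6 sets the missing-data rules:
- Under 5% missing: complete cases.
- 5% or more, and Little's test points to data missing completely at random: complete cases.
- 5% or more, and judged missing at random: multiple imputation. "The missing outcome measures will be imputed using Allocation Group and Stratification factors (Site) and other variables that are deemed to be predictors of missingness". The listed candidate predictors are demographic, clinical and cognition variables; the other visit's score is not among them.
- Above 40%: "if more than 40% of data is missing for an outcome measure the data will not be imputed". The fallback is a complete-case result that is to be read with caution.

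Two other statements bear on this. SAP section 4 says "All those randomised will be included in the analysis", on an intention-to-treat basis. Protocol section 6 says "a maximum-likelihood multiple imputation approach will be used with a sensitivity comparison of complete case dataset", and gives no ceiling.

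**The concern.** Under these rules a participant with a 3-month but no 6-month score drops out of any complete-case 6-month analysis, and the named imputation variables make no use of the 3-month score either. Yet that score is probably the best available predictor of the missing one. Above 40% missing, complete cases become the only analysis, although the protocol gives them the role of sensitivity comparison. The caveat on interpretation changes the wording of the report, not the estimate or its error rate.

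Dropout that differs by arm is plausible. Participants know their allocation (protocol 7.3), and one arm has ten sessions over three months while the other has usual care (protocol 5.2.2). If those who stop after 3 months differ by arm in how they were doing, the 6-month comparison is distorted, and data already collected could correct much of that.

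**Working it through.** **The plan's own figures.** A two-sample t-test for 0.7 SD, two-sided 5%, 90% power needs 43.87 per arm, so 44:44 = 88. For 25% attrition, 88 / (1 - 0.25) = 117.3, so 118. Both figures in SAP 4.1 reproduce.

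**What the 40% rule means.** With 120 recruited, 0.40 × 120 = 48, so the rule needs at least 49 missing and leaves at most 71 analysed. Planned loss is 25%, or 30 people. Assume that those missing at 3 months stay missing, and that 0 to 30 are missing at 3 months. Then 49 - 30 = 19 to 49 - 0 = 49 participants have a 3-month score that the 6-month analysis does not use.

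**How the bias arises.** Assume that baseline correlates 0.4 with both visits and that the two visits correlate 0.7. Given baseline, the slope of the 6-month on the 3-month score is (0.7 - 0.4 × 0.4) / (1 - 0.4²) = 0.54 / 0.84 = 0.64. Complete-case bias is then roughly 0.64 times the between-arm difference in the stayers' mean baseline-adjusted 3-month residual. A bias of 0.15 SD needs a difference of 0.15 / 0.64 = 0.23 SD; 0.31 SD needs 0.31 / 0.64 = 0.48 SD.

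**Simulation.** From the SAP: 118 randomised 1:1, 5% two-sided tests. Assumed, because the documents give no figures: 20% missing at 3 months, 45% at 6 months, the correlations above, a 3-month effect of 0.7 SD and no 6-month effect. Complete-case analysis adjusted for baseline was compared with the maximum-likelihood estimate from both visits.

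| Dropout after 3 months | Complete-case bias (SD) | False positives |
|---|---|---|
| Random | 0 | 5% |
| Depends on 3-month score alike in both arms | -0.04 to -0.06 | about 6% |
| Depends on it in one arm (log-odds 0.7 to 1 per SD) | 0.10 to 0.15 | 7-10% |
| Opposite directions by arm (log-odds 0.5 to 1 per SD) | 0.16 to 0.31 | 11-28% |

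The joint model was unbiased in the random, one-arm and opposite-direction scenarios, with false positives of 4-5.5%. The biases in the last two rows are sizes; their sign depends on who leaves.

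**Power for a true 0.4 SD effect at 6 months.** Under random dropout, 39% for complete cases against 44% for the joint model. With one-arm dropout (log-odds 0.7), complete-case power was 25% against 44% when the bias ran against the intervention. When poorer-scoring intervention participants left, complete-case rejection rose to about 62%.

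**In BGSI points**, using the SDs of 1.74 and 2.86 in the protocol's power calculation:
- One arm: 0.10 × 1.74 = 0.17 to 0.15 × 2.86 = 0.43.
- Opposite directions: 0.16 × 1.74 = 0.28 to 0.31 × 2.86 = 0.89.

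**Is the ceiling the cause?** A second simulation took 120 participants, all seen at 3 months, about 45% missing at 6 months, an effect of 0.7 SD and 3-to-6-month correlations of 0.5 to 0.8. Complete-case bias was about 0 when dropout depended only on baseline, +0.12 to +0.25 SD for intervention-arm dropout and +0.26 to +0.50 SD for opposite directions. Imputation without the 3-month score gave the same bias as complete cases. Imputation with it was within 0.01 SD in every scenario.

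**The case against.** The strongest reply has five parts.

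- *The rule may never apply.* Planned attrition is 25%, and no 6-month loss figure is given. The SAP also does not say whether the 40% is counted per visit: pooled over visits, 20% and 45% average 32.5% and would not trigger it. This stands as a limit on the ceiling, but not on the point as a whole, because the 3-month score goes unnamed below 40% too.
- *The SAP cites published guidance and asks for caution.* Both are true. But the guidance is cited for not imputing, and a likelihood model over both visits imputes nothing.
- *The larger figures need dropout tied to the 3-month score differently by arm, and a 0.7 SD effect that has vanished by 6 months.* Correct. The worst case, 0.89 points, is also under half the protocol's 2-point important difference.
- *The list of imputation predictors is open, so the 3-month score could be added.* It could, which is why the point is that the score is not explicitly used.
- *The joint model is not a cure.* When dropout depended on the unseen 6-month score differently by arm, its bias was 0.15-0.32 SD, against 0.26-0.54 SD for complete cases. It reduces the problem and does not remove it.

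A reader might also infer that the primary result is exposed. The documents do not support that here: a participant whose 3-month score is missing has no 3-month score to discard.

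**Conclusion.** The point holds for 6-month outcomes. It is a cheap improvement to exploratory analyses rather than the correction of an error. Under the stated assumptions, complete-case bias is 0.10-0.15 SD for one-arm dropout and 0.16-0.31 SD for opposite directions. It is small or nil if dropout is random, depends only on model covariates, or acts alike in both arms; random dropout still costs about five percentage points of power.

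A reader might infer that the 40% ceiling creates the bias, or that the outcome with most missing data must have the most biased estimate. Neither follows. The same exposure exists below 40%, so lifting the ceiling alone would change little, and the amount of bias depends on who leaves, not only on how many. Separately, the complete-case-only rule above 40% does not fit the protocol's missing-data approach or the SAP's commitment to analyse everyone randomised, and these should be reconciled.

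**What to change.** 1. In SAP 4.6, remove the switch to complete cases as the only analysis above 40%.
2. At every level of missingness, analyse continuous 6-month outcomes with one likelihood mixed model over the 3- and 6-month scores: arm by visit, baseline by visit, site, the SAP 6.6 covariates, and unstructured within-person covariance. Multiple imputation done by arm and including the other visit's score is an alternative.
3. For the binary DSQ-PEM, use imputation that includes the other visit's value, then the planned logistic model, so that the odds ratio being estimated does not change.
4. Keep complete cases as a sensitivity analysis. Keep the caution on interpretation above 40%, and state that the percentage is counted per visit.
5. Add a simple missing-not-at-random sensitivity analysis, for example shifting imputed 6-month scores by arm over a stated range.

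The cost is some SAP wording, a slightly larger model for this sample size, and a little more analysis work across the 6-month outcomes. No new data are needed, and the 3-month primary analysis can stay as written.

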#### **4.7 ASSUMPTION CHECKING**

All assumptions relating to the models will be checked and evaluated whether appropriate to use with the data. If any of the assumptions are substantially violated, then appropriate non-parametric tests will be conducted.

During data cleaning, the Trial Statistician will assess the data for outliers by running Grubbs test (Grubbs 1969) and visually inspecting a boxplot. Any outliers identified will

be queried to identify whether the outlier is a data entry error, a measurement error or to confirm that it is a genuinely unusual value. Once this has been clarified the data will be amended if necessary or will remain unchanged if identified to be correct. No outliers will be discarded from analysis if they are within range a.

The distribution of the continuous data will be checked and depending on the result of these checks a decision will need to be made as to whether a transformation should be applied to the data and if so, which transformation should be used. If a transformation is required, the distribution of the transformed data will be checked. Analysis will be reported on the original scale, transforming data back. If a transformation is inappropriate/unhelpful then nonparametric analysis methods will be considered.

For the logistic regressions, if detection rates (number of responses observed) are very low, where appropriate, either a Firth's Bias-Reduced Logistic Regression will be conducted, or descriptive statistics reported.

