### **4.1 SAMPLE SIZE JUSTIFICATION**

A sample of 88 (44:44) will be required to detect an effect of 0.7 on the BGSI at 3 months with 90% power at a 5% significance level. Incorporating an attrition of 25% will require recruitment and randomisation of 118 participants (59:59). Therefore, 120 participants will be recruited from the same clinics. Participants in WS1 can if desired take part in WS2.

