### **4.3 LEVELS OF CONFIDENCE AND P-VALUES**

All statistical tests will be two-sided and performed using 5% level of significance. All confidence intervals presented will be 95%, unless stated otherwise.

Secondary outcomes will not be adjusted for multiple comparisons, as standard. The primary outcome is powered for at the significance level stated. Analysis of all secondary outcomes is considered exploratory, and any statements of results related to these outcomes will be reported appropriately.

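### SAP 4.7 lets an assumption check move the primary analysis from the adjusted BGSI mean difference to an unnamed rank test or a transformed model; the adjusted difference should stay primary, with a robust or bootstrap interval

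*Combined protocol and SAP*

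**What the plan says.** SAP 6.6 sets the primary analysis: a mixed linear regression of 3-month BGSI attainment with site as a random effect and gender, age, years of education and baseline RBANS as fixed factors. It adds: "Baseline BGSi attainment score will also be incorporated to account for any differences at baseline". The same section promises unadjusted and adjusted results with 95% confidence intervals. Protocol 6 is broader: "All treatment effect estimates will be presented with 95% confidence intervals".

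SAP 4.7 covers every model and holds two rules that do not quite agree.

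- Its opening paragraph: "If any of the assumptions are substantially violated, then appropriate non-parametric tests will be conducted".
- A later paragraph has the distribution of the continuous data checked and a transformation chosen if needed, and continues: "Analysis will be reported on the original scale, transforming data back". If transformation does not help, non-parametric methods are only to be considered.

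The section names no test, no transformation, no threshold for a substantial violation, and no effect estimate or interval for either fallback. The later rule checks the data rather than the model residuals. Robust standard errors are not mentioned anywhere, and bootstrapping appears only in the protocol's health economic analysis.

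**The concern.** Followed literally on the primary outcome, SAP 4.7 changes what the trial estimates. The planned result is an adjusted mean difference in BGSI points with a confidence interval. An ordinary rank test cannot carry site, baseline BGSI, age, gender, education and baseline RBANS, and it yields no mean difference. A transformed model can carry them, but its treatment effect is on another scale.

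The form of the primary result would also be settled after the outcome data had been inspected, against no stated threshold. The outcome is the mean of three goals, each rated 1 to 10 (SAP Appendix 2). Floor or ceiling effects could therefore prompt a switch, although the documents give no basis for saying how likely that is.

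Multiple imputation adds a further gap. SAP 4.6 can call for it once 5% of data are missing, and 25% attrition is planned for. Nothing says how a rank test would be combined across imputed datasets.

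**Working it through.** **1. The plan's own figures.** Inputs are in SAP 4.1 and 4.3 and Protocol 7.1 (Power calculation): effect 0.7, 90% power, two-sided 5%, 1:1 allocation, 25% attrition, a 2-point difference.

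- Normal approximation: n per arm = 2(1.960 + 1.282)²/0.7² = 42.9, so 43.
- Two-sample t-test: 43.87, so 44 per arm and 88 in all, as stated; power at 44 per arm is 90.1%.
- Attrition: 88/0.75 = 117.3, so 118, as stated.
- SD: 2/0.7 = 2.857 (stated as about 2.86); 2.857/1.74 = 1.64, consistent with the stated increase of about 65%.

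These figures reproduce and are not in dispute. They describe an unadjusted comparison of two means.

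**2. What each route delivers.**

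| Route | 6.6 covariates | Effect measure | 95% CI for a difference in points |
|---|---|---|---|
| Mixed model (SAP 6.6) | kept | adjusted mean difference | yes |
| Ordinary rank test | lost | none in points | no |
| Rank test with Hodges-Lehmann interval | lost | unadjusted shift | unadjusted only |
| Log-transformed model | kept | ratio | not by back-transformation |

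In a simulated 1-10 score with a true mean difference of about 1.9 points, the back-transformed log coefficient was a ratio of about 1.6. Such a ratio has no single value in points: it is 0.6 × 3 = 1.8 points from an assumed control level of 3, and 0.6 × 5 = 3.0 from an assumed level of 5.

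**3. Precision.** The half-width is 1.96 × SD × √(2/44) × √(1 − r²), where r is the correlation of baseline with 3-month BGSI. The documents do not give r, so a range is assumed.

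- Unadjusted: 1.96 × 2.857 × 0.2132 = 1.19 points.
- r = 0.3: 1.19 × 0.954 = 1.14.
- r = 0.5: 1.19 × 0.866 = 1.03.
- r = 0.7: 1.19 × 0.714 = 0.85.

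The unadjusted interval is thus about 5%, 15% or 40% wider.

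**4. Power on normal data.** By normal approximation, the standardised effect is 0.7/0.2132 = 3.283.

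- Rank test, efficiency 0.955: Φ(3.283 × √0.955 − 1.96) = 89.4%, whatever r is.
- Adjusted model: Φ(3.283/√(1 − r²) − 1.96) = 93.1%, 96.6% and 99.6% for r = 0.3, 0.5 and 0.7.

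**5. Whether the model can be kept.** These are simulations at 44 per arm with illustrative error shapes. Site, where included, was fitted as an indicator; the full mixed model was not fitted.

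- *HC3 robust intervals, normal, exponential and heavy-tailed (t, 3 df) errors:* coverage 95-97%, null rejection 4.3-4.6%.
- *Single bounded 1-10 score, four sites, 600 replicates:* HC3 coverage 95-96%, half-widths 1.07, 0.98 and 0.82 for r = 0.3, 0.5 and 0.7. Percentile bootstrap (resampled within arm) coverage was 93.5-94.3%. The unadjusted Hodges-Lehmann half-width stayed at about 1.15.
- *Three-goal means of 1-10 ratings, including floor and ceiling skew:* power 85-97% for the adjusted model with HC3 errors against 85-89% for Mann-Whitney; HC3 null rejection 3.6-5.5%.
- *Unbounded exponential or heavy-tailed errors, r = 0.3:* Mann-Whitney 97.6-98.3% against about 91% for the adjusted model. At r = 0.7 the order reverses, 92-93% against 99%.

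**The case against.** **The adjusted estimate may not be lost.** A reader might infer that the fallback is bound to drop adjustment and the interval. The documents do not support that. SAP 4.7 names no test, so a covariate-adjusted rank method or a Hodges-Lehmann interval is not excluded. It does not say that the tests replace the model, and the promise of adjusted results in SAP 6.6 carries no condition. What stands is that 4.7 does not say which result is primary once a check fails.

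**Transformation is the milder case.** A reader might also infer that it discards the covariates or the precision. It does not: a transformed model keeps both covariates and an interval. A difference in points could even be rebuilt from model predictions, but SAP 4.7 describes only transforming back.

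**A rank test is not always weaker.** The sample size assumed no baseline adjustment, so the rank test on normal data falls only about one percentage point short of the planned 90%. With strongly skewed or heavy-tailed errors and a weak baseline correlation it can be clearly better, at about 98% or more against 91-92% at r = 0.3. This stands in full. It came from unbounded error shapes, which a mean of three bounded ratings does not resemble.

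**Blinding limits the harm.** Protocol 7.3 and SAP 2 keep the statistician blind to allocation until the SAP's blinded analyses are done, so selection towards a favoured arm is unlikely. The choice would still follow inspection of outcome data.

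**Conclusion.** The concern holds as a matter of what is estimated and pre-specified. If SAP 4.7 is triggered on the primary outcome and an ordinary rank test is used, the trial has no adjusted difference in BGSI points with the promised interval. If a log model is used, it has an adjusted ratio instead.

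The cost in precision is an interval about 5% to 40% wider, for an assumed r of 0.3 to 0.7 and the planning SD of 2.857. For bounded three-goal means, the adjusted model with robust errors has power about equal to or higher than the rank test's. No general claim of lost power is justified.

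A reader might infer that the trial plans to judge the between-arm estimate against 2 points. No section says so: 2 points appears in the power calculation and in the individual responder definition of SAP 6.8.

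The problem is conditional on a check failing, and its likelihood is unknown. It bears on the primary result, though, and is cheap to remove, so the SAP should be changed.

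**What to change.** Replace the fallback rules in SAP 4.7 with wording to this effect:

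- The adjusted mean difference from the SAP 6.6 model is the primary result whatever the residual checks show.
- If residuals are materially non-normal or heteroscedastic, its 95% confidence interval is taken either from participant-level HC3-type robust errors, with site as an indicator and no clustering on the few centres, or from a participant bootstrap stratified by site and arm. The SAP should name one in advance; HC3 had the better coverage in the simulations.
- If multiple imputation is used, the robust or bootstrap standard error is obtained within each imputed dataset and then pooled.
- Non-linearity is handled by changing the form of the covariate, since robust intervals do not cure it and a rank test does not address it.
- Rank-based or transformed analyses of the primary outcome are sensitivity analyses only.
- If a secondary outcome is log-transformed, a ratio of geometric means is reported with its interval.

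The cost is a short SAP amendment and modest extra code, rather more if the bootstrap is combined with imputation. It needs no new data and no change in sample size. There are two downsides. The robust-error option fits site as an indicator rather than as the random effect in SAP 6.6. And with strong skew and a weak baseline correlation the rank test may be the more powerful analysis, which is why it is kept as a sensitivity analysis.
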